### **3.0 Describe procedures, treatment, or activities that are above or in addition to standard practices in this study area (eg. extra medical or health-related procedures, curriculum enhancements, extra follow-up, etc):**

SRS-22 and Spinal appearance questionnaires, surface topography and radiograph scanning (which will be extracted from the hospital database) are standard practices at the specialized Scoliosis Clinic. The data routinely collected at scoliosis clinic visits will be used in the study. Clinics are routinely scheduled every 6 months for patients meeting the eligibility criteria in our study.

Our 3 months assessment is additional to the routine visits. Some tests at baseline, 3 and 6 months are additional to routine visits and all exercise treatments are additional to routine visits.

Participating in the study requires completing tests and questionnaires in addition to usual procedures. Physical examination at baseline, 3 and 6 months including range of motion of back and lower extremity are not current practice. The following questionnaires completed at baseline, 3 and 6 months are extra procedures, too: Demographic/History, Pain rating and diagram, 3D Physical activity recall, Self-efficacy and Global Rating of

Change.

All exercise visits are additional to routine scoliosis visits.

- 4.0 If the proposed research is above minimal risk and is not funded via a competitive peer review grant or industry-sponsored clinical trial, the REB will require evidence of scientific review. Provide information about the review process and its results if appropriate.**  
 Glenrose Hospital Foundation, Clinical Research Grant Review Committee (completed)  
 Scoliosis Research Society, Small Exploratory Grant Review Committee (completed 2009 and 2010)  
 Women's and Children Health Research Institute, CIHR Pre-review Process (completed)  
 SickKids Foundation New Investigator Review committee (awarded in 2013, completed also in 2010)

- 5.0 For clinical trials, describe any sub-studies associated with this Protocol.**

ID: Pro00043397

Pro00043397

Status: Approved

2.2 Research Methods and Procedures

## 2.2 Research Methods and Procedures

*Some research methods prompt specific ethical issues. The methods listed below have additional questions associated with them in this application. If your research does not involve any of the methods listed below, ensure that your proposed research is adequately described in Section 2.1: Study Objectives and Design or attach documents in the Documentation Section if necessary.*

- 1.0 \* This study will involve the following (select all that apply)**  
 Surveys and Questionnaires (including internet surveys)  
 Radiation: Any test or procedure that may involve exposure to radiation (including screening chest x-ray)

*NOTE 1: Select this if you are directly collecting health information as part of your protocol OR will be conducting a chart/record review/reviewing health data secondarily. This includes anonymized or identifiable health information.*

*NOTE 2: Select this option if this research ONLY involves analysis of blood/tissue/specimens originally collected for another purpose but now being used to answer your research question. If you are enrolling people*

*into the study to prospectively collect specimens to analyze you **SHOULD NOT** select this box.*

*NOTE 3: This section is intended to reflect the secondary use of non-health data. Do **NOT** select this if you are using data that originally came from health sources, i.e., anonymized administrative data.*

ID: Pro00043397

Pro00043397

Status: Approved

2.9 Surveys and Questionnaires (including Online)

## 2.9 Surveys and Questionnaires (including Online)

- 1.0 **How will the survey/questionnaire data be collected (i.e. collected in person, or if collected online, what survey program/software will be used etc.)?**  
Participants will be asked to complete questionnaires at home and bring them to the appointment with them.
- 2.0 **Where will the data be stored once it's collected (i.e. will it be stored on the survey software provider servers, will it be downloaded to the PI's computer, other)?**  
Paper in locked file cabinet in room 6-107 and entered in REDCAP.
- 3.0 **Who will have access to the data?**  
PI and study team members.
- 4.0 **If you are using a third party research tool, website survey software, transaction log tools, screen capturing software, or masked survey sites, how will you ensure the security of data gathered at that site?**

ID: Pro00043397

Pro00043397

Status: Approved

2.20 Radiation Safety

## 2.20 Radiation Safety

- 1.0 Will your research involve any of the following? (Check all that apply)**  
X-rays of the skull, facial bones, neck, spine, thorax, abdomen, pelvis or hip
- 2.0 Research involving exposure of participants 0-17 years of age to any amount ionizing radiation, regardless of how little, must be approved by the AHS Regional Radiation Safety Committee (RSC). Will your research involve exposure to participants aged 0-17 years to any amount of ionizing radiation?**  
☒ Yes ☐ No

**Pro00043397**

**3.1 Risk Assessment**

**Status:** Approved

### 3.1 Risk Assessment

**1.0 \* Provide your assessment of the risks that may be associated with this research:**

Minimal Risk - research in which the probability and magnitude of possible harms implied by participation is no greater than those encountered by participants in those aspects of their everyday life that relate to the research (TCPS2)

**2.0 \* Select all that might apply:**

| Description of Possible Physical Risks and Discomforts |                                                                                                |
|--------------------------------------------------------|------------------------------------------------------------------------------------------------|
| Possibly                                               | Participants might feel physical fatigue, e.g. sleep deprivation                               |
| No                                                     | Participants might feel physical stress, e.g. cardiovascular stress tests                      |
| Possibly                                               | Participants might sustain injury, infection, and intervention side-effects or complications   |
| Possibly                                               | The physical risks will be greater than those encountered by the participants in everyday life |

| Possible Psychological, Emotional, Social and Other Risks and Discomforts |                                                                                                                                                                                 |
|---------------------------------------------------------------------------|---------------------------------------------------------------------------------------------------------------------------------------------------------------------------------|
| Possibly                                                                  | Participants might feel psychologically or emotionally stressed, demeaned, embarrassed, worried, anxious, scared or distressed, e.g. description of painful or traumatic events |
| Possibly                                                                  | Participants might feel psychological or mental fatigue, e.g. intense concentration required                                                                                    |
| Possibly                                                                  | Participants might experience cultural or social risk, e.g. loss of privacy or status or damage to reputation                                                                   |
| No                                                                        | Participants might be exposed to economic or legal risk, for instance non-anonymized workplace surveys                                                                          |
| Possibly                                                                  | The risks will be greater than those encountered by the participants in everyday life                                                                                           |

**3.0 \* Provide details of all the risks and discomforts associated with the research for which you indicated YES or POSSIBLY above.**

- For physical assessment:

We do not expect adverse effects to result from the study physical assessment. All the procedures are routinely used in the assessment of patients with scoliosis and are considered non-invasive. In the unlikely event where we would detect a spinal deformity warranting further investigation in the otherwise healthy teenagers, we will provide

information on the nature of our findings and suggest referral to the patient's family physician. We do not expect that subjects will suffer any side-effects from the physical assessment in this study. The assessment involves simple movements and tests. Participants should not feel pain in this study. Rarely, participants may feel sore during the first few days following a simple physical assessment. For those experiencing soreness it should disappear in a few days. The tests are not invasive and do not use radiation. There could be other side-effects which it is not possible to anticipate.

- For the treatment:

Schroth exercises are designed to improve the ability to maintain correct posture through endurance and strength training. Schroth exercises include de-rotation, de-flexion, and stretching exercises to establish vertebral alignment, torsional respiration exercises, and strengthening exercises for the abdominal, back, leg and foot muscles, and as such are not expected to have any adverse effects on patients. The exercises involve simple movements and positioning. Participants should not feel pain in this study. Rarely, participants may feel sore during the first few days following trying a new exercise. For those experiencing soreness it should disappear in a few days.

- For the surface topography:

The full torso scanning procedure involves removing clothes of the torso, hiding the breast using stick-on bra and having some reference points marking on the skin. Some participants may feel uncomfortable with their torso exposed.

-In both study groups, some patient's scoliosis may progress to the extent where bracing or surgery prescription criteria are met.

Due to the COVID-19 pandemic, there is a possibility of infection transmission with additional visits to the lab and human interactions the context of the research.

#### **4.0 \* Describe how you will manage and minimize risks and discomforts, as well as mitigate harm:**

- We do not expect adverse effects to result from the study. All the procedures are routinely used in the assessment of patients with scoliosis and are considered non-invasive. In the unlikely event where we would detect a spinal deformity or a pathology warranting further investigation, we will provide information on the nature of our findings and suggest referral to the patient's family physicians. We will be available to discuss our findings with the physician at the patient's request. Testing procedure can be interrupted at the patient's request at anytime.

- The surface topography scanning procedures are all done by a female. The subjects will be oriented to the scanning area. Participants will be instructed in the use of the stick-on bras. The evaluator will then leave the patient in the closed off scanning area to disrobe privately and apply the bras. The patient will be given a hospital gown for privacy when the

evaluator returns to apply the reference marks on the skin and to adjust the positioning frame. The evaluator will then leave again and the patient will disrobe. The surface scan will be obtained immediately. During the scan the subject will be offered to be accompanied by a family member or a friend if they desire. The scanner operator will be a female. The analysis of the scan will be done by a female and the head will be cropped off of the scan to protect patient privacy. Patients may refuse to participate at any point.

- Schroth therapist will individually instruct all the patients in the execution of the exercises in the first 5 sessions, and the group sessions will be led by a Schroth therapist. All exercises can be modified to minimize possible discomfort that can be caused by inadequate level of intensity.

- In the case of patient's scoliosis progression to the extent where bracing or surgery prescription criteria are met, they will be referred to their treating surgeon and prescribed treatment deemed appropriate. SRS prescription criteria will be used.

For exams, participants will be invited to complete questionnaires at home to minimize visit duration. All exams will occur in CSB to avoid visiting too many sites which would increase their risk of exposure to COVID 19. The EHS plan for [name] lab requires a clear AHS Covid-19 screen for both patients and therapist.

For patients the requirements are as follows: strict control of building access, not allowing accompanying person access in the lab unless assistance is needed, patients are required to wear disposable mask provided by the lab, and patients are required to wash their hands before and after the exam. For the therapist, requirements are as follow: required to wear disposable mask, visor, gown and gloves, have a clear Covid 19 screen and wash hands before and after each patient.

Our evaluation equipment and clinic room will be cleaned and disinfected as per our EHS return to work plan before and after every patient. We will space exams at least one 1 hour apart to allow time for this cleaning and minimize interactions between different people accessing the lab. The number of persons in the lab is tightly controlled with a maximum of 3 including patient for the exam (with routine generally being only the examiner and the patient).

The few participants receiving therapy will be given a choice to come to CSB for therapy in person (individual (not groups)) or online via secure videoconference.

**5.0 Is there a possibility that your research procedures will lead to unexpected findings, adverse reactions, or similar results that may require follow-up (i.e. individuals disclose that they are upset or distressed during an interview/questionnaire, unanticipated findings on**

MRI, etc.)?

☐ Yes ☒ No

- 6.0** If you are using any tests in this study diagnostically, indicate the member(s) of the study team who will administer the measures/instruments:

| Test Name | Test Administrator | Organization | Administrator's Qualification |
|-----------|--------------------|--------------|-------------------------------|
|-----------|--------------------|--------------|-------------------------------|

There are no items to display

- 7.0** If any research related procedures/tests could be interpreted diagnostically, will these be reported back to the participants and if so, how and by whom?

ID: Pro00043397

Pro00043397

3.2 Benefits Analysis

Status: Approved

### 3.2 Benefits Analysis

- 1.0** \* Describe any potential benefits of the proposed research to the participants. If there are no benefits, state this explicitly:  
There are possible benefits for the participants in this study. There is evidence that suggests Schroth exercises can improve spinal curvature, slow the progression of scoliosis, correct posture, and increase strength in some patients with AIS. The benefits are not guaranteed and patients that have received Schroth exercise treatment in the past have not always had these results. If findings from the evaluations suggest that you need additional medical attention, you will be contacted and referred appropriately.
- 2.0** \* Describe the scientific and/or scholarly benefits of the proposed research:  
- Results of our study will help determine whether this exercise treatment is appropriate to implement at the Edmonton Scoliosis clinic as an alternative to standard practice (observation/ or bracing) for the smaller curves (10-45 degrees according to Cobb).  
- Results of our study may also help other clinics in the world to decide whether they want to offer Schroth treatment.
- 3.0** If this research involves risk to participants explain how the benefits outweigh the risks.  
Risks are minimal and controlled. The results could potentially have great

benefit for clinical practice by providing evidence for the conservative treatment for adolescent idiopathic scoliosis and assist physicians in prescribing exercises to the right patient.

With our careful mitigation procedures for COVID-19 risk, the benefits are potentially important.

**ID:** Pro00043397**Pro00043397**

4.1 Participant Information

**Status:** Approved

### 4.1 Participant Information

1.0

**\* Will you be recruiting human participants** (*i.e. enrolling people into the study, sending people online surveys to complete*)?

☒ Yes ☐ No

**1.1 Will participants be recruited or their data be collected from Alberta Health Services or Covenant Health or data custodian as defined in the Alberta Health Information Act?**

☒ Yes ☐ No

**1.2 Would you like to include information about this study on the Be The Cure searchable database?**

☐ Yes ☐ No

**ID:** Pro00043397**Pro00043397**

4.2 Additional Participant Information

**Status:** Approved

### 4.2 Additional Participant Information

1.0

**Describe the participants that will be included in this study. Outline ALL participants** (*i.e. if you are enrolling healthy controls as well*): Patients with Adolescent Idiopathic Scoliosis (AIS), with juvenile idiopathic scoliosis (JIS), or syringomyelia without chiari from the Specialized Scoliosis Clinic in Edmonton, Calgary, and Montréal (n=208 total). They are between 10 and 16 years old.

## 2.0 **\* Describe and justify the inclusion criteria for participants (e.g. age range, health status, gender, etc.):**

Patients with Adolescent Idiopathic Scoliosis (AIS), with juvenile idiopathic scoliosis (JIS), or syringomyelia without chiari from the Specialized Scoliosis Clinic in Edmonton, Calgary, Montréal (n=208) will be recruited from our scoliosis clinics. AIS is defined as idiopathic scoliosis diagnosed between the ages of 10-16. JIS is defined as idiopathic scoliosis diagnosed between the ages of 5-10. Idiopathic scoliosis may have appeared between the ages of 5-10, but not been diagnosed until after the age of 10. Therefore, including patients with JIS and AIS in the study is not including two distinct forms of scoliosis, rather a continuum of idiopathic scoliosis. Patients with syringomyelia without chiari are common and does not exclude a patient's diagnosis as AIS or JIS.

Only females are targeted. Females are more frequently severely affected to levels justifying a treatment prescription. Other inclusion criteria are:

(1) magnitude of spinal curve 10° to 45° (Cobb angle),  
 -Larger curves meet the clear indication recommended by the Scoliosis Research Society to be prescribed surgery. Small curves in skeletally immature adolescents have higher risk of progression. Curves over 30° are more likely to progress after skeletal maturity. European consensus for conservative treatment recommends exercises alone below 20° and exercises in combination with a brace for patients with curves greater than 20°.

(2) may be treated with or without brace  
 -We have broadened inclusion criteria to be inclusive of all conservative treatment offered at the Specialized scoliosis clinic in Edmonton, Calgary and Montréal (observation and bracing). European consensus for conservative treatment recommends exercises alone below 20° and exercises in combination with a brace for patients with curves greater than 20°. Including patients with and without brace treatment allows for comparison of exercise alone and in combination with brace treatment. Including brace treatment as a potential predictor of treatment success is representative of decisions clinicians are making in the treatment of patients with scoliosis. We will examine whether bracing in combination with exercises is predictive of success beyond the other treatment combinations.

(3) Risser 0-3 (indicating Incomplete skeletal maturity)  
 -Patients with curves over 30° have a risk of progression beyond skeletal maturity. Schroth exercises are recommended for all curve sizes.

(4) age 10-16  
 -Patients are treated between the ages of 10-18 at the Edmonton Scoliosis Clinic. Inclusion of patients over the age of 10 allows for comprehension of Schroth exercise program. Limiting upper limit of age range to 16 increases the likelihood that the patients are skeletally immature and therefore still truly at risk of progression. Patients having reached the skeletal maturity are simply given a recommendation to exercises but the prescription would be deemed optional in most cases.

The SickKids reviewers requested we enroll skeletally immature patients only.

- (5) ability to travel to study sites at least weekly.
  - To ensure that we can assess the efficacy of the proposed exercise protocol we require the participant to attend weekly exercise sessions at the study sites. This will ensure feasibility of the trial with opportunity for maximal compliance.

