**Schroth Exercise Trial for Scoliosis**

**Background**

Adolescent Idiopathic Scoliosis (AIS), a 3D spinal deformity, is the most common orthopedic condition in adolescents requiring elective surgery and affects mostly females. In mild scoliosis from  $10^{\circ}$  to  $25^{\circ}$  the ratio is 4:1, in moderate AIS from  $25^{\circ}$  to  $50^{\circ}$  the ratio is 7:1, while in severe AIS  $>50^{\circ}$  the ratio is 10:1. Scoliosis reduces quality-of-life, often results in pain, poor function and self-image.

Usually, curves between  $25^{\circ}$ - $45^{\circ}$  are prescribed a brace and curves over  $45^{\circ}$  are treated surgically. Smaller curves are not treated. The

Schroth method utilizes asymmetric 3D endurance, strength and breathing exercises aiming to correct posture and scoliotic curves. Schroth therapists provide support by skillful resistances, auxiliary handholds, and specific verbal instructions and feedback from mirrors. Schroth exercises aim to restore proper physiological three-dimensional alignment.

Schroth treatment has proven effective in improving strength, posture, slowing progression and improving Cobb angle in many cohort studies. However, these results have not yet been tested in RCTs.

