### **Objectives**

To conduct a RCT on the effect of Schroth exercises for AIS compared to the current treatment standard (observation or bracing prescribed as per SRS guidelines). Specific objectives are to compare the effects of 6-month of Schroth exercises added to standard care to standard care alone on curve severity measured using the Cobb angle, and on secondary outcomes including quality-of-life, spinal appearance, objective posture and spinal muscle endurance measurements. We will also compare the effect of 6 months of Schroth therapy offered to control participants after completing 6 months in the standard care group and determine if effects can be maintained until maturity once supervision is terminated.

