#### Schroth exercises:

Patients for which the SRS guidelines would recommend observation as standard of care will do exercises alone. Patients for which the SRS guidelines would recommend bracing will do exercises in addition to being prescribed a brace.

*Private sessions-* During the first 2 weeks, patients will attend 5 1-hour-long individual sessions to learn Schroth principles, exercises and correct breathing, and to confirm independent adequate performance with a checklist.

*Home exercises-* A 30-min. daily home exercise program of 3 to 4 exercises will be adjusted during the first 6 months using an algorithm. Compliance will be monitored using a logbook for 6 months. Completion exercises during the last 12 months will also be monitored using a logbook.

*Group Sessions-* Classes increase compliance. Patients will attend weekly 1-hour-long group therapist-led exercise classes. Adequate

exercise performance will be assessed using the checklist. Pain will be monitored.

*Algorithm* – An algorithm guides exercise prescription, intensity and progression from static to dynamic execution. Prescription begins with easier exercise. If performed adequately, a more challenging exercise will be tried. If performance is inadequate, an easier exercise will be attempted. Exercises performed adequately will be prescribed.

At follow-up, if performance is adequate, dosage will increase to target intensity. Target intensity increases repetitions aimed to enhance endurance. Final tension intensity is nearly maximum isometric contraction held in corrected posture.

During the COVID-19 pandemic, the few participants still receiving exercises will be offered the choice to receive therapy in person or via videoconference. Our therapist [name] has access to a secure videoconferencing system (JaneApp) to deliver this therapy remotely. Alternatively [name] has access to a secure ZOOM space. No recording is made during the videoconferencing session.

Controls: Controls will receive the standard of care appropriate for their curves (observation or bracing prescribed as per SRS guidelines), and will complete baseline, 3 and 6 months exams. After 6 months they will cross-over to the treatment group.

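### Bracing is not randomised, so the planned comparison of exercise alone with exercise plus brace is confounded by indication, and the trial cannot show Schroth to be an alternative to bracing

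*Protocol*

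**What the plan says.** Protocol section 2.1, Objectives, defines the trial's question as the effect of six months of "Schroth exercises added to standard care to standard care alone on curve severity measured using the Cobb angle".

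The Schroth exercises part of section 2.1 sets bracing by guideline in both arms:
- Schroth arm, observation indicated: "Patients for which the SRS guidelines would recommend observation as standard of care will do exercises alone".
- Schroth arm, brace indicated: "Patients for which the SRS guidelines would recommend bracing will do exercises in addition to being prescribed a brace".
- Control arm: "Controls will receive the standard of care appropriate for their curves (observation or bracing prescribed as per SRS guidelines".

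The Background links the indication to curve size: curves of 25° to 45° usually "are prescribed a brace and curves over" 45° go to surgery, while smaller curves are left untreated.

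Two statements go beyond this design. Section 4.2, item 2.0, criterion (2), says "Including patients with and without brace treatment allows for comparison of exercise alone and in combination with brace treatment" and then announces: "We will examine whether bracing in combination with exercises is predictive of success beyond the other treatment combinations". Section 3.2, item 2.0, says the results will help decide whether Schroth is suitable "as an alternative to standard practice (observation/ or bracing) for the smaller curves", which it gives as 10° to 45°.

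**The concern.** Criterion (2) presents the mix of braced and unbraced patients as a strength that permits a treatment comparison. The guideline creates that mix, not the randomisation. Braced exercisers will on the whole have started with larger curves. If curve size predicts change in the outcomes, the two groups will differ even when the brace adds nothing to the exercises, or a real difference may be hidden. A reader would take the result as evidence for or against combining the treatments.

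The wording in section 3.2 carries a second risk. Patients with a brace indication have a brace in both arms. A positive result would show that Schroth adds something to the brace. It would say nothing about whether Schroth could take its place.

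**Working it through.** **1. What is randomised.** The section 2.1 rules give four cells:

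| Care indicated at entry | Schroth arm | Control arm |
|---|---|---|
| Observation | exercises alone | observation |
| Brace | exercises + brace | brace |

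Comparisons across a row are randomised. Comparisons down a column are by indication. So exercises alone versus exercises + brace is not randomised. Of the three comparisons of the combination with the other cells, only the one with brace alone is randomised. No cell holds a patient with a brace indication who receives Schroth without a brace.

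**2. The plan's own figure.** Section 4.2, item 5.0, gives 129 per group for an effect size of 0.31, one-sided alpha 0.05 and 80% power. With 1.645 + 0.842 = 2.487, n = 2 × 2.487² / 0.31² = 128.7, so 129. This reproduces exactly. It covers the Schroth-versus-control comparison only.

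**3. How large the confounding could be (illustration).** Assumptions: curve size uniform on 10° to 45°, brace from 25° upward, no true brace effect.
- Braced share: 20/35 = 57%.
- Mean curve: 35° braced and 17.5° unbraced, a gap of 17.5°.
- SD of curve size: 35/√12 = 10.1°, so the gap is 17.5/10.1 = 1.73 SD.
- If baseline curve correlates r with outcome change, the spurious difference is 1.73 × r: 0.17 SD at r = 0.1, 0.35 SD at r = 0.2, 0.52 SD at r = 0.3.

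The last two exceed the trial's design effect of 0.31. With 104 Schroth patients, the chance of a false finding at two-sided 5% is about 14%, 42% and 75%. Under so strict a threshold the groups have no curve sizes in common, and covariate adjustment would rest on extrapolation.

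**4. Precision of what the design can give.** Let s be the braced share and n the number per group, with s equal in both arms. Smallest detectable effects at one-sided 0.05 and 80% power, in SD units:
- Within a stratum holding share p of the patients: 2.487 × √(2/(np)).
- Arm-by-brace interaction: 2.487 × √(2/(ns) + 2/(n(1−s))).

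| n per group | s | Schroth effect, braced | Schroth effect, unbraced | Interaction |
|---|---|---|---|---|
| 129 (104 + 25 pilot) | 0.5 | 0.44 | 0.44 | 0.62 |
| 129 (104 + 25 pilot) | 0.3 | 0.57 | 0.37 | 0.68 |
| 104 (this study only) | 0.5 | – | – | 0.69 |
| 104 (this study only) | 0.3 | – | – | 0.75 |

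Example: n = 129, s = 0.5 gives 2.487 × √(2/64.5 + 2/64.5) = 2.487 × 0.249 = 0.62. Power for an interaction as large as 0.31 SD would be about 34% (s = 0.5) or 31% (s = 0.3) with 129 per group.

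**The case against.** The two sentences in criterion (2) justify an inclusion criterion. They are not an objective, and the Analyses part of section 2.1 specifies no braced-versus-unbraced test. The same paragraph calls bracing a possible predictor of success, which is acceptable as exploratory work, and its modelling may be left to an SAP that is not at hand. Comparing the combination with all the other combinations could even be done with an arm-by-brace model. Section 3.2 is a benefits statement, and Objectives describes the add-on design correctly.

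Much of this is fair, and it limits the point to wording and interpretation. It does not remove the point. The protocol says that the design allows the comparison and that the question will be examined, without a caveat, and no SAP can turn a guideline prescription into a randomised factor.

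Three stronger readings are tempting, and the documents do not support them:
- *That no part of the alternative wording can stand.* Among patients with an observation indication, exercises alone versus observation is the randomised comparison. Only the bracing part lacks support.
- *That the arm-by-brace interaction isolates a combination effect.* The Schroth effect within each stratum is randomised. The difference between strata is not: if Schroth works differently in larger curves, the interaction will show it. Adjusting for the main effect of baseline Cobb angle does not remove this.
- *That bracing follows curve size strictly.* The Background says usually, and the SRS criteria are not reproduced. Some overlap in curve size is possible, so the amount of confounding cannot be established from the protocol.

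**Conclusion.** The point stands for two statements. The comparison of exercise alone with exercise plus brace, and of the combination with the non-randomised cells, is confounded by indication. The trial also cannot show that Schroth is an alternative to bracing. The quantities that randomisation supports are the Schroth-versus-control effects within patients with and without a brace prescription at entry.

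The size of any bias is unknown. The 0.17 to 0.52 SD above is an illustration that depends on the assumed curve distribution, the strict threshold and the assumed correlations. The detectable interaction of 0.62 to 0.68 SD with 129 per group is at least twice the design effect of 0.31. It assumes a braced share of 50% or 30% and equal variances.

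A reader might infer that the main result is compromised. It is not: the Schroth-versus-control comparison is randomised whether or not patients wear a brace, and its sample size reproduces.

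**What to change.** In section 4.2, criterion (2), replace the two sentences with the following: the Schroth-versus-control effect will be estimated separately in patients with and without a brace prescription at entry, adjusted for baseline Cobb angle; the arm-by-brace interaction will be reported as exploratory; a difference between the strata may reflect curve size and not an effect of combining brace and exercise. Brace status should be the one at entry, because section 3.1 foresees that patients in either group may meet bracing criteria during the study, and grouping by later status would break the randomised comparison. Test other predictors of success in the same way, as interactions with randomised arm.

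In section 3.2, item 2.0, remove bracing from the alternative wording and describe Schroth as an addition to bracing where a brace is indicated. The reference to observation can stay.

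The cost is a few sentences and one interaction term. Treatment, recruitment and the primary analysis do not change. The drawback is low precision, so the stratum results should be given as estimates with confidence intervals, and a non-significant interaction should not be read as equal benefit.
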